## 2. Materials and Methods

### 2.1. Study Design and Setting

The SWITCHtoHEALTHY study is a parallel, randomized, single-blinded, and controlled multicentric nutritional intervention study. It aims to evaluate the effects of a multi-component intervention deployed at the family level, combining digital interactive tools and hands-on educational materials and activities with healthy and sustainable plant-based snacks, on the adherence to the MD pattern in 480 families with adolescents and children from three Mediterranean countries (Spain, Turkey, and Morocco), with 160 families per country. Secondarily, the effects of the multi-component intervention will be assessed according to lifestyle, anthropometric, dietary, sociodemographic, socioeconomic, and environmental indicators.

This study protocol was registered at ClinicalTrials.gov (NCT06057324) and is in accordance with the Helsinki Declaration and the Good Clinical Practice Guidelines on the International Conference of Harmonization. All the procedures described in the protocol, informed consent, and other documents have been reviewed and approved by the Ethics Committees of the three centers involved in the study: (1) Fundació Eurecat (study co-ordinator): Institut d’Investigació Sanitària Pere Virgili, IISPV (Ref. 135/2023); (2) Ethics Committee of Bursa Uludag University Faculty of Medicine Clinical Researches (Ref. 2023-23/29); and (3) Comité d’Ethique pour la Recherche Biomédicale (CERB), Université Mohammed V Faculté de Médecine et de Pharmacie de Rabat (preapproval). This protocol complies with the Standard Protocol Items: Recommendations for Clinical Trials (SPIRIT 2013 Statement and SPIRIT-AI extension) [32,33].

The 160 families recruited in each country will be randomly assigned into eight study groups (*n* = 20 families per group per country) according to a multi-component intervention including different combinations of the three study components (artificial intelligence (AI)-based app for all family; educational materials and empowerment activities for adolescents; and healthy plant-based snacks for children) and a control group that will receive basic Mediterranean guidelines for parents and their children (Figure 1).

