### 2.7. Sample Size

The sample size was calculated based on differences in MD adherence score (primary outcome) measured by MEDAS and KIDMED questionnaires. The sample size was estimated using the analysis of variance (differences between 8 study groups). It was assumed that the alpha value would be equal to 0.05 and beta 0.20, exactly as reported in previous studies [61], with a common standard deviation equal to 1.19. The minimum group size needed to detect a minimum increase of 1 point in the intervention group’s MEDAS compared to the control group is equal to 45 families per study group (15 families per country). The total sample is, therefore, 45 × 8 = 360 families. However, assuming a 25% drop-out rate, the minimum group size is equal to 60 families per study group (20 families per country). Overall, 160 families will thus be recruited per country after obtaining the approval of the Ethics Committee of each recruiting center and written informed consent from parents and adolescents.

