### 2.10. Statistical Analysis

#### 2.10.1. Univariate Data Analysis

The data obtained from families in this study will be evaluated via an intention-to-treat (ITT) analysis, including data from families who drop out of the study, and per protocol (PP), that is, those families who have completed the treatment plan and who have exactly followed the instructions of the trial protocol. The error level of 0.05 will be set as a limit of statistical significance. A data analysis will be performed using the Statistical Software for Data Science (STATA, College Station, TX, USA) version 17.0 [63].

Mean and standard deviation will be reported for normally distributed variables and quantiles (25th percentile, median, and 75th percentile) for non-normally distributed variables. The Kolmogorov–Smirnov test and the Shapiro–Wilk test will be used to test for the normality of variables. The resulting scores of adherence to the MD (measured from the MEDAS and KIDMED questionnaires) will be used to calculate the mean differences between each intervention group and the control group before (V1) and after interventions (V2). Multiple comparisons (V2 vs. V0 and V2 vs. V1) of mean differences before and after interventions will be undertaken to assess the independent effect of interventions. The normality of the differences will be checked and, depending on the results, the following contrasts will be performed: parametric statistics (three-factor ANOVA with post hoc tests using the Bonferroni correction and considering the interactions between the following factors: app, educational materials, and snack products) will be used for normally distributed variables to compare differences in means and nonparametric statistics (Kruskal–Wallis test) will be used for non-normally distributed variables. Lineal regression and Spearman’s method will be used to test for correlations between normal and non-normal outcome variables, respectively.

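### The main ANOVA on change scores names neither country nor the baseline score, which costs precision, and it tests V2–V0 and V2–V1 without ranking them, which raises the false-positive rate

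*Protocol article*

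**What the plan says.** All references are to the protocol article.

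- **Outcome analysed.** Section 2.10.1 works on differences between visits: "The normality of the differences will be checked and, depending on the results, the following contrasts will be performed".
- **Model.** For normally distributed variables it is a "three-factor ANOVA with post hoc tests using the Bonferroni correction", "considering the interactions between the following factors: app, educational materials, and snack products". No other term is named.
- **Time contrasts.** "Multiple comparisons (V2 vs. V0 and V2 vs. V1) of mean differences before and after interventions will be undertaken". Neither is called primary.
- **Error level.** "The error level of 0.05 will be set as a limit of statistical significance". Bonferroni is tied to the post hoc tests of the ANOVA and is not extended over the two time contrasts.
- **Allocation.** Section 2.1: "The 160 families recruited in each country will be randomly assigned into eight study groups", with 20 families per group per country, repeated in Section 2.7. Section 2.6 says that randomisation is stratified and blocked but does not name the stratum.
- **Country elsewhere.** Section 2.10.2 plans a stratified look at socioeconomic and cultural context. It sits under the multivariate analysis and does not adjust the main test.
- **Baseline scores.** Section 2.4 records MEDAS and KIDMED at V1. A V0 score is implied by the eligibility cut-off of 11 in Section 2.2 and by the V2 versus V0 comparison.

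**The concern.** There are two separate problems with different consequences.

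**Precision.** If allocation is balanced within country, any country difference in change is unrelated to group. A model without country leaves that difference in the error term. Snacks and materials are adapted by country (Sections 2.3 and 2.3.3), so such differences are plausible. A change score also fixes the weight of the baseline at one, whereas a covariate model estimates that weight and in large samples never does worse with the same baseline.

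**Error and ambiguity.** V0 precedes randomisation. V1 comes later, after allocation and after Phase 1, during which adolescents in the education groups join cocreation sessions on the Mediterranean diet (Section 2.3.2). Group-specific training also takes place at V1. The two contrasts can therefore disagree, and the plan does not say which one decides.

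Most exposed are the comparisons of single groups with control, the interactions, and effects smaller than the planned 1 point. The factorial design in Section 2.1 exists partly to estimate these.

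**Working it through.** **1. The plan's own figure.** Section 2.7 gives a difference of 1 MEDAS point, "with a common standard deviation equal to 1.19", alpha 0.05, beta 0.20 and 45 families per group. The article does not show its formula. One route that returns 45 is a two-sided normal approximation with Bonferroni over all 28 pairs of 8 groups:

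n = 2(z₁ + z₂)²·SD²/δ² = 2 × (3.124 + 0.842)² × 1.19² / 1² = 44.5, so 45.

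Then 45/0.75 = 60, 45 × 8 = 360 and 60 × 8 = 480, all as stated. On this route the whole 0.05 goes to the pairs within one ANOVA, and none is set aside for a second time contrast.

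**2. Baseline score.** Assume equal variance s² at both visits and correlation rho, which the article does not give.

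- Var(change) = 2s²(1 − rho)
- Var(V2 adjusted for that baseline) = s²(1 − rho²)
- Ratio = (1 + rho)/2

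| rho (assumed) | Ratio | Families giving the precision of 45 | Extra families a change score needs |
|---|---|---|---|
| 0.4 | 0.70 | 31.5 | 43% |
| 0.5 | 0.75 | 33.8 | 33% |
| 0.6 | 0.80 | 36.0 | 25% |
| 0.7 | 0.85 | 38.3 | 18% |
| 0.8 | 0.90 | 40.5 | 11% |

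**3. Country.** If country explains a share R2 of the variance in change, adding it multiplies the error variance by 1 − R2: 0.98, 0.95, 0.90 and 0.80 at assumed R2 of 0.02, 0.05, 0.10 and 0.20. With balanced allocation, leaving it out makes the nominal 0.05 test conservative. The true level is 2[1 − Φ(1.96/√(1 − R2))] = 0.048, 0.039 and 0.028 at R2 of 0.02, 0.10 and 0.20.

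**4. Both together.** Take rho 0.5 within country, R2 0.10, SD 1.19, 360 evaluable families and a main effect of 0.3 points.

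- Change score without country: SD = 1.19/√0.90 = 1.254; SE = 2 × 1.254/√360 = 0.132; power = Φ(0.3/0.132 − 1.96) = 0.62.
- V2 with baseline and country: SD = 1.19 × √0.75 = 1.031; SE = 0.109; power = 0.79.

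A simulation with 15 families per group per country gave the same values.

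**5. Two unranked contrasts.** V2–V0 and V2–V1 share V2. With equal variances and one common rho, their covariance is s²(1 − rho) and each variance is 2s²(1 − rho), so they correlate 0.5 whatever rho is. The chance of at least one two-sided result below 0.05 under no effect, from the bivariate normal, is:

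- correlation 0.5: 9.1%
- correlation 0.7: 8.3%
- independence: 1 − 0.95² = 9.75%, the ceiling

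In simulation at rho 0.5, the rate was 9.0% with no country effect and 7.3% with country R2 of 0.10 left in the error term.

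**6. Which baseline.** Step 2 compares methods on the same baseline only. If V0 correlates 0.4 with V2 and V1 correlates 0.6 (assumed), adjustment for V0 gives s²(1 − 0.16) = 0.84s². The V2–V1 change has 2s²(1 − 0.6) = 0.80s². Adjustment for V0 then beats the V2–V0 change (1.20s²) but not the V2–V1 change.

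**The case against.** The article condenses a fuller protocol, and covariates and the ranking of contrasts are often settled in an analysis plan. The factor list can be read as naming the factors whose interactions are examined, not as excluding all other terms. That is fair, so the point is that the text names no such terms, not that it rules them out. It does, however, commit to a specific model and to two specific contrasts.

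The same section describes V1 as before and V2 as after the intervention, which leans towards V1 to V2 as the main comparison. It does not say so, and it lists V2 versus V0 alongside.

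A change score already cancels stable differences in level between countries; only differences in change remain. This stands, and it is why R2 is taken in the change and may be small.

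Stronger readings that the documents do not support:

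- **That omitting country inflates error.** Step 3 shows the opposite.
- **That the error rate reaches 18.5%** (1 − 0.95⁴, for two contrasts on two scores). This needs four independent tests and a rule that success on either score suffices. The contrasts share V2, the scores come from the same families, and no such rule is stated.
- **That the trial is underpowered for its main effects.** These compare about 180 with 180 evaluable families, and power for 1 point at SD 1.19 is essentially 1. Nor does Section 2.7 say whether 1.19 is the SD of a raw or a change score, so no shortfall against plan can be shown.
- **That V1 is clearly contaminated.** Two cocreation sessions of about 12 adolescents reach about 24 of the 80 education-group families per country (4 groups × 20), if no more sessions are held and attendees differ. The risk is real but partial.

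**Conclusion.** The point holds in two parts.

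**Precision:** as described, the model gives up 10% to 30% of the variance by using change scores in place of adjustment for the same baseline (rho 0.8 to 0.4), and a further 2% to 20% by leaving out country (R2 0.02 to 0.20). Neither rho nor R2 is in the article, so these are assumed ranges. Country as the stratum is an inference from the fixed numbers per country and group.

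**Error:** two unranked contrasts at 0.05 give about 8% to 9% per effect at correlation 0.7 to 0.5, and somewhat less if country variance stays in the error term, which partly offsets the excess without being a substitute for control.

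Neither part threatens a 1-point main effect. The change is worth making because it is nearly free and settles which result decides.

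**What to change.** In Section 2.10.1, name one primary analysis: the V2 score in a linear model with app, educational materials, snacks and their interactions, country as a fixed effect, and one named baseline score as covariate. State the stratification factor in Section 2.6 so that model and randomisation agree.

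V0 is the clean choice of baseline because it precedes randomisation. If V1 is preferred for its likely closer correlation with V2, say so, and state the risk that it already carries some effect of allocation or of the cocreation sessions. Label the other time contrast supportive.

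If success on either MEDAS or KIDMED is meant to count, the plan would have to say so before a correction across the two scores is called for.

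The cost is wording and slightly more analysis work. No visit or family is added, and the V0 score is already presupposed, although Section 2.4 should list it among the V0 measurements. The downside is that V0 may correlate less with V2 than V1 does, which would reduce the gain in precision.

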#### 2.10.2. Multivariate Data Analysis

Structural equation modeling (SEM) is a multivariate, hypothesis-driven technique that is based on a structural model representing a hypothesis about the causal relations among several variables. It will integrate the multiple factors affecting the adherence to the MD, including economic factors, social factors, psychological factors, quality of life, attitudes and beliefs related to food, health and healthy lifestyle, dietary habits, nutritional knowledge, and physical activity. It will test the direct and indirect effects of these multiple factors on the adherence to the MD. Fit indices like the root mean square error of approximation (RMSEA), the Tucker–Lewis index (TLI), and the comparative fit index (CFI) will be used to check for the adequacy of the fit of the model.

We will monitor model fit indices (RMSEA, TLI, and CFI) to ensure they fall within acceptable ranges and adjust the SEM model structure as necessary based on theoretical and statistical considerations to maintain interpretability. Missing data will be handled using Full Information Maximum Likelihood (FIML) estimation, an approach suited to SEM that reduces bias by using all available data without directly imputing values. Additionally, we will evaluate patterns of missingness to determine if data are missing at random (MAR) or missing not at random (MNAR) and will justify our handling approach accordingly. The reliability will be checked using three criteria, including the internal consistency, composed reliability, and average variance extracted (AVE). Cronbach’s alpha coefficient will be used to test the internal consistency of the scales. For validity, two criteria will be tested, including the convergent validity and the discriminant validity [62].

To address the socioeconomic and cultural differences among participants from Spain, Turkey, and Morocco, a stratified analysis will be conducted to examine the impact of socioeconomic and cultural contexts on participants’ responses to the interventions. By categorizing participants based on key demographic variables such as income, education level, and cultural background, we can gain insights into how these factors influence dietary behaviors and adherence to the MD.

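### The SEM's fit indices both steer changes to the model and serve as its adequacy check on the same data, so acceptable final fit is weak evidence for the causal model

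*Protocol article*

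**What the plan says.** All of this is in section 2.10.2, Multivariate Data Analysis, of the protocol article.

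- The SEM is introduced as a "hypothesis-driven technique that is based on a structural model representing a hypothesis about the causal relations among several variables".
- Its purpose is inferential: "It will test the direct and indirect effects of these multiple factors on the adherence to the MD".
- RMSEA, TLI and CFI "will be used to check for the adequacy of the fit of the model".
- In the next paragraph the same three indices are monitored "to ensure they fall within acceptable ranges and adjust the SEM model structure as necessary based on theoretical and statistical considerations". The sentence ends with the aim of keeping the model interpretable, so the full condition on changes reads "based on theoretical and statistical considerations to maintain interpretability".
- Internal consistency, composite reliability and average variance extracted are also planned. "For validity, two criteria will be tested, including the convergent validity and the discriminant validity".

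No data set is set aside for checking a modified structure.

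**The concern.** A fit index tests a hypothesised structure only if the structure was chosen without looking at that index on those data. Here acceptable fit is first a target to be reached by changing the model and then the evidence that the model is adequate. A reader of the results could not tell whether good fit reflects the hypothesis or the adjustments.

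The SEM carries the trial's explanatory claims. The abstract promises to identify what drives behaviour change, section 2.5 wants these reasons in order to scale up or redesign interventions, and the Discussion foresees policy recommendations. A path model tuned to the data but reported as a confirmed hypothesis could mislead those uses. Paths added because they improve fit on these data also do not have p-values with their usual meaning.

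**Working it through.** **No plan figure to reproduce.** The article gives no number for the SEM. The sample sizes below come from section 2.7: 45 × 8 = 360 evaluable families, and 45 / (1 − 0.25) = 60 per group, so 60 × 8 = 480 recruited. Using families as N is an assumption.

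**Formulas.** Take 10 observed variables: the nine question blocks of Table 3 plus adherence. For a recursive path model fitted by maximum likelihood:

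- F = Σ ln(residual variance of each equation) − ln|S|, where S is the correlation matrix, and χ² = (N − 1)F
- df = 10 × 9 / 2 − paths = 45 − paths
- RMSEA = √[max(χ² − df, 0) / (df(N − 1))]
- CFI = 1 − max(χ² − df, 0) / max(χ²₀ − df₀, χ² − df)
- TLI = (χ²₀/df₀ − χ²/df) / (χ²₀/df₀ − 1), where subscript 0 is the independence model and df₀ = 45

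**What a change does.** Freeing a path cannot raise χ². RMSEA (while χ² > df) and TLI depend on the current model through χ²/df, and (χ² − Δ)/(df − 1) < χ²/df exactly when Δ > χ²/df. A useless path can therefore worsen them, but a search that picks the path with the largest Δ tends to improve them. RMSEA ≤ 0.06 requires χ²/df ≤ 1 + 0.0036(N − 1). This is 1 + 0.0036 × 359 = 2.29 at N = 360 and 1 + 0.0036 × 479 = 2.72 at N = 480. An unlimited search can run to the saturated model, where χ² = df = 0 and fit is perfect.

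**Simulated pass rates of wrong models.** Passing means RMSEA ≤ 0.06, CFI ≥ 0.95 and TLI ≥ 0.95. In the true model each possible path is present with probability 0.45 and size 0.15 to 0.40. Mildly wrong models take the true one, swap neighbours in the causal order 3 (or 5) times and omit 3 (or 5) paths (400 replicates). Badly wrong models are drawn without regard to the truth (300 replicates). The admissible share is a random subset of absent paths, standing in for a limit set by theory. Ranges cover N = 360 and 480.

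| Changes allowed | 3 swaps, 3 omitted | 5 swaps, 5 omitted | Badly wrong |
|---|---|---|---|
| None | 0–0.5% | 0% | 0% |
| Any path, no limit | 100% | 100% | 100% |
| Half of absent paths, no limit | 27% | 9–12% | 0–0.3% |
| A quarter, no limit | 5–8% | 1% | 0% |
| Any path, at most 3 (badly wrong: 5) | 91.5–93% | 8.5–16% | 0–0.3% |
| Half, at most 3 (badly wrong: 5) | 25–26% | 2% | 0–0.3% |

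**Effect on p-values for adherence.** In a further simulation adherence was independent of all nine factors, which were correlated with each other. Of about 9 to 30 paths added to reach acceptable fit, on average only 0 to 0.6 pointed to adherence. If the starting model already held all nine direct paths to adherence, false positives per path were 4 to 6%, which is nominal. With sparse starting structures they were about 9 to 23%. The article does not give the starting structure.

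**The case against.** A reader might infer that the fit check cannot fail and that a wrong causal model is certain to pass. The text does not support that. Changes must rest on theory as well as statistics and must keep the model interpretable, and a search limited in this way can end without acceptable fit, as the lower rows of the table show. The 100% rate describes an unrestricted search, which the article does not announce. The reliability and validity checks can also fail, although they concern the measurement scales and not the causal paths.

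Nor does the article say that the initial model's fit will go unreported, or that retained paths will be tested as though fixed in advance. Cut-offs and a list of permitted changes may stand in a fuller document, and their absence here is no fault. Respecification guided by theory is common SEM practice, and the distortion of p-values for adherence can be nil.

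All of that stands, and it limits the size of the problem. It does not remove the stated rule. The theory condition sets no stopping point and does not say that a model that still fits poorly will be reported as such, while the declared aim is to bring the indices into range. An analysis plan that followed the sentence faithfully would carry the same circularity.

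**Conclusion.** The point holds as a minor one. Section 2.10.2 uses the same indices to steer the SEM and to certify it. Acceptable fit after changes is then weak evidence for the hypothesised causal structure, and tests of direct and indirect effects in a modified model are exploratory.

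The size cannot be fixed from the article. Under the assumed structures and cut-offs, respecification raised the pass rate of wrong models from 0–0.5% to between 0 and 93% with limits on the changes, and to 100% only without any limit. False positives per path to adherence ranged from nominal to about 23%, depending on the starting model.

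The comparison of randomised groups on MEDAS and KIDMED is the three-factor ANOVA of section 2.10.1 and is not touched. Separately, models with reversed arrows but the same implied covariances fit equally well, so fit indices do not establish causal direction even without any adjustment.

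**What to change.** Replace the sentence in section 2.10.2 on monitoring the indices and adjusting the structure with:

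*The prespecified model is fitted first and its RMSEA, TLI and CFI are reported whatever their values. Any later change is listed with its theoretical reason, and the modified model is reported beside the original, labelled exploratory, without confirmatory p-values.*

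Modifying the model on V1 data and confirming it on V2 data would not be a sound substitute. Both visits use the same families, so V2 is not an independent sample. V2 also follows interventions meant to change the factors in the model, so misfit there could have legitimate causes.

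The cost is wording and one model fit on data already being collected. The downside is that the prespecified model may have to be reported as fitting poorly.
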